### Recruitment strategies

2.10

Recruitment will follow a dual-pathway strategy combining proactive identification by the research team with voluntary engagement by potential participants. Investigators will identify potentially eligible patients through routine clinical pathways, including inpatient and outpatient oncology records, multidisciplinary tumor board documentation, and postoperative follow-up clinics. To improve recruitment efficiency, each study site will also conduct standardized online and offline recruitment activities through professional medical websites, hospital homepages, official social media accounts, recruitment posters, and informational brochures distributed in relevant departments such as thoracic surgery, oncology, and psychosomatic medicine. Potentially eligible individuals who express interest in participation will be contacted by trained research personnel and provided with detailed study information. After written informed consent is obtained, eligibility will be confirmed through standardized screening and baseline assessments. Recruitment progress will be regularly monitored across all sites, and additional site-level support or recruitment optimization measures will be implemented when necessary to ensure timely enrollment of the target sample size.

### Randomization

2.11

A total of 468 participants will be enrolled from nine research centers, with 52 participants planned for each center. Randomization will be stratified by study center and by whether paroxetine is initiated after enrollment, with 20 participants in the non-paroxetine stratum and 32 participants in the paroxetine stratum at each center. Within each stratum, participants will be randomly assigned in a 1:1 ratio to receive either MSNP granules or placebo granules. The random allocation sequence will be generated by an independent statistician using computer software and restricted block randomization. Details of the block size and other restriction procedures will be kept in a separate confidential document unavailable to personnel responsible for enrollment or intervention assignment. The randomization sequence will correspond to sequentially numbered study medication codes. After eligibility confirmation and written informed consent, participants will receive the next available medication code according to their study center and paroxetine stratum.

### Blinding

2.12

Trial participants, care providers, outcome assessors, and data analysts will remain blinded to treatment allocation throughout the study. Unblinding will only be permitted in cases of serious adverse events requiring urgent clinical intervention and must be approved by the principal investigator. In all other cases, treatment allocation will remain concealed until completion of the trial and finalization of data analysis. At the end of the 6-week treatment period and before unblinding, blinding assessment will be performed among participants, care providers, and outcome assessors. They will be asked to guess the treatment allocation as “MSNP,” “placebo,” or “uncertain” and to provide the reason for their guess where applicable. The results of the blinding assessment will be summarized descriptively to evaluate the success of blinding.

### Data collection and management

2.13

Study data will be documented on customized, paper-based case report forms (CRFs) developed specifically for this trial. Information to be collected includes baseline demographic data and clinical characteristics (e.g., duration of depressive symptoms, depression severity, tumor stage, and time since surgery), treatment adherence, scheduled outcome evaluations, laboratory data, and safety-related events. At each site, trained research personnel will collect data in accordance with a standardized operating procedure manual to ensure procedural consistency. Prior to study initiation, all research staff will undergo centralized training covering CRF documentation, clinical scale scoring (e.g., HAMD-17, PHQ-9, GAD-7), adverse event logging, and source verification protocols. To encourage compliance and reduce missed follow-ups, participants will receive visit schedules in advance and be contacted regularly throughout the study.

Following data entry onto CRFs, trained staff will transcribe information into a centralized electronic data capture system with secure, role-based login credentials. The system features automated logic checks, completeness validation, timestamped audit trails, and alerts for anomalous or missing data. A dual-entry process will be implemented to minimize data discrepancies. Ongoing central monitoring will be conducted by the data management team, who will review data submissions, issue queries when necessary, and track resolution in accordance with pre-established data handling procedures. All data will be anonymized using coded identifiers, and identifying information will not be included in the analytical dataset. Original paper records will be retained in locked, access-restricted locations at each site. Encrypted digital data will be regularly backed up, and all trial records will be archived for at least 5 years post-completion. Data security and protocol compliance will be overseen by the institutional review boards of all participating centers.

### Statistical analysis

2.14

All efficacy analyses will be performed according to the intention-to-treat (ITT) principle in all randomized participants. Safety analyses will be conducted in all participants who initiate protocol-defined treatment. Missing outcome data will be handled using multiple imputation under the missing-at-random assumption.

The primary outcome (total effective rate) will be analyzed using a log-binomial regression model to estimate the adjusted RR and corresponding 95% confidence interval (CI) between the intervention and control groups. The model will include study center and concomitant paroxetine use as covariates. An interaction term between treatment group and paroxetine use will be included to assess the potential moderating effect of antidepressant co-administration on the intervention effect. Sensitivity analyses will include a predefined per-protocol (PP) analysis to assess the robustness of the findings. The PP population will include participants who complete the entire treatment course without major protocol violations and have available primary outcome data. Prespecified subgroup analyses will be performed according to baseline sex (male vs. female), age (≤55 vs. >55 years), depression severity (mild vs. moderate), NSCLC stage (I vs. II vs. III), and KPS score (70–80 vs. 90–100).

For other outcomes, repeated-measures continuous variables such as HAMD-17, PHQ-9, and GAD-7 scores will be analyzed using linear mixed-effects models to evaluate longitudinal changes from baseline between groups. The models will include group, time, group-by-time interaction, and baseline score as fixed effects, and participant and study center as random effects. For single-timepoint continuous variables such as inflammatory markers and neurotransmitters, between-group comparisons will be conducted using independent-samples t-tests or Mann–Whitney U tests, depending on data distribution. For time-to-event outcomes including PFS and OS, Cox proportional hazards models will be used to estimate hazard ratios and 95% CIs, adjusting for study center and paroxetine use. For categorical outcomes such as AE incidence and depression remission rate, group comparisons will be conducted using the chi-square test or Fisher’s exact test, as appropriate.

All statistical analyses will be performed using SPSS version 26.0 and R version 4.3.1. A two-sided p-value ≤ 0.05 will be considered statistically significant for the primary outcome. No adjustment for multiplicity is planned for secondary outcomes, and these analyses will be regarded as exploratory. No interim analyses are planned for this trial.

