According to this meta-analysis, in the non-paroxetine stratum, the expected total effective rates were 59.6% for MSNP alone and 37.0% for placebo alone, corresponding to a projected risk ratio of 1.61. In the paroxetine stratum, the expected total effective rates were 91.6% for MSNP plus paroxetine and 79.0% for placebo plus paroxetine, corresponding to a projected risk ratio of 1.16. Using the “Tests for Two Proportions” module in PASS version 21, with a two-sided alpha of 0.05, 80% power, equal allocation within each stratum, and an assumed dropout rate of 15%, the required sample sizes were 180 participants for the non-paroxetine stratum and 288 participants for the paroxetine stratum. Therefore, the final total sample size was set at 468 participants. In the non-paroxetine stratum, 90 participants will receive MSNP alone and 90 will receive placebo alone. In the paroxetine stratum, 144 participants will receive MSNP plus paroxetine and 144 will receive placebo plus paroxetine. Overall, 234 participants will receive MSNP-containing interventions (intervention group), and 234 participants will receive the corresponding placebo-containing control interventions (control group).

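### With fixed center terms and the plan's own response rates, the log-binomial primary model reaches its boundary in most trials, and its usual confidence interval is too narrow in the paroxetine stratum

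*Protocol article*

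**What the plan says.** Section 2.14 (Statistical analysis) names one primary method: "The primary outcome (total effective rate) will be analyzed using a log-binomial regression model to estimate the adjusted RR", with a 95% confidence interval. On its terms: "The model will include study center and concomitant paroxetine use as covariates". And further: "An interaction term between treatment group and paroxetine use will be included". The same section handles missing outcomes by multiple imputation and names center as a random effect only for the mixed models of continuous scores. For the primary model, fixed center indicators are therefore the plain reading.

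Section 2.9 (Sample size estimation) gives the rates. Without paroxetine, "the expected total effective rates were 59.6% for MSNP alone and 37.0% for placebo alone". With paroxetine, "the expected total effective rates were 91.6% for MSNP plus paroxetine and 79.0% for placebo plus paroxetine".

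Section 2.11 (Randomization) gives the layout: "A total of 468 participants will be enrolled from nine research centers, with 52 participants planned for each center". Each center is to contribute 20 participants without and 32 with paroxetine, randomized 1:1, so 10 and 16 per arm.

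**The concern.** The log link does not keep fitted probabilities below 1, so the fit has to be restricted. In the paroxetine stratum under active treatment the expected rate is already 0.916. A center only 1/0.916 = 1.09 times the average reaches 1, and with 52 participants per center chance alone can produce that. When the maximum lies on the limit, the score equations are not solved there, standard software has trouble, and the theory behind Wald standard errors no longer applies. Multiple imputation repeats the difficulty in every imputed dataset.

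This is the trial's confirmatory analysis. At stake is either an estimator chosen after the specified one has failed, or a confidence interval that is too narrow in the stratum holding 288 of the 468 participants.

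**Working it through.** **Inputs.** Nine centers; 10 per arm without and 16 per arm with paroxetine in each (section 2.11). Rates 37.0% and 59.6% without, 79.0% and 91.6% with paroxetine (section 2.9). Model: intercept, treatment, paroxetine, treatment x paroxetine, eight center indicators (section 2.14).

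**1. The plan's own figure.** The plan states: "the required sample sizes were 180 participants for the non-paroxetine stratum and 288 participants for the paroxetine stratum". Per arm, n = [1.96 sqrt(2 p q) + 0.84 sqrt(p1 q1 + p2 q2)]^2 / (p1 - p2)^2, where p is the mean rate and q = 1 - p, then division by 0.85 for dropout.
- Non-paroxetine: 76 per arm; 76/0.85 = 89.4, so 90 per arm and 180 in total. Reproduced.
- Paroxetine: 123 per arm; 123/0.85 = 144.7, so 145 per arm and 290 in total, against 288 stated. The difference is trivial.

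So the rates above are the ones that the design rests on.

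**2. Chance of full cells.** P(16 of 16 respond) = 0.916^16 = 0.246. P(at least one such center among nine) = 1 - (1 - 0.246)^9 = 0.92. A full cell does not by itself force the boundary, because the model shares terms across cells, so the model was fitted.

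**3. Where the maximum lies.** Constrained maximum likelihood on simulated trials; boundary means that the largest fitted probability reaches 1.

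| Setting | Trials | Boundary |
|---|---|---|
| Interaction, no center differences | 2,000 | 82.3% |
| No interaction, no center differences | 1,000 | 86.8% |
| Interaction, 15% missing | 1,000 | 86.0% |
| Interaction, center SD 0.3 (logit) | 1,000 | 84.6% |
| No interaction, center SD 0.3 | 1,000 | 88.3% |

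With the center terms removed, the boundary occurred in 0 of 40 runs, so the center terms drive it.

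**4. Standard fitting.** An emulation of the R routine (IRLS with step-halving, valid starting values, first setting) gave, in 2,000 trials: 1,263 not converged (63%), 208 stopped at the boundary (10%) and 529 reported as converged (26%). Of those 529, 261 had their true maximum on the boundary. A genuine interior fit was thus reached in 268/2,000 = 13%. SPSS, also named in the article, was not emulated.

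**5. If a constrained fit is forced (interaction model).** Mean RRs were 1.62 and 1.17, against true values 0.596/0.370 = 1.61 and 0.916/0.790 = 1.16. Coverage of the 95% Wald interval from expected information, the kind IRLS reports:

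| Setting | RR without paroxetine | RR with paroxetine |
|---|---|---|
| No center differences | 94.8% | 90.5% |
| 15% missing | 95.4% | 90.5% |
| Center SD 0.3 | 94.6% | 88.6% |

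The shortfall is not confined to boundary trials. In the first setting coverage was 92.0% among the 1,645 boundary trials, leaving (1,810 - 1,513)/355 = 84% among the interior ones. That split conditions on the data, so it is only indicative.

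**6. Without the interaction term.** The constrained common RR averaged 1.20, against 1.26 from modified Poisson. At the plan's rates the pooled RR is [(90 x 0.596 + 144 x 0.916)/234] / [(90 x 0.370 + 144 x 0.790)/234] = 0.793/0.628 = 1.26.

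**7. Comparator.** Modified Poisson with robust variance, same data and terms: mean RRs 1.62 and 1.16, coverage 94.6% and 95.0% (94.9% and 95.3% with center SD 0.3).

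**8. Sensitivity to the rates.** Smaller runs kept 37.0/59.6% and lowered the paroxetine-stratum rates. The boundary frequency fell to about 50-57% at 75/87%, 12-20% at 70/81% and 2-4% at 60/72%.

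**The case against.** The strongest reply has four parts.

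- **A boundary maximum is still a maximum-likelihood estimate.** This stands. A reader might infer that the model cannot be fitted, or that the RR would be missing or biased. The constrained RRs are nearly unbiased in the planned model, so that reading fails. One can also produce a 100% failure rate from R's default starting values, but that reflects the starting values and not the model. Nor does the 1.20 against 1.26 show boundary bias: inverse-variance weighting of the two stratum log RRs (variances 0.0265 and 0.0025) already gives exp[(0.477/0.0265 + 0.148/0.0025)/(1/0.0265 + 1/0.0025)] = 1.19. The gap is mainly one of weighting when a single RR is fitted to two different ones.
- **Better intervals exist.** In part. A likelihood-ratio interval for the paroxetine RR covered 92.2% (500 trials, Monte Carlo SE about 1.2 points), and a Wald interval from observed information covered 97.3%. Coverage then depends on an implementation choice, while the robust alternative is close to 95% without it.
- **The rates may not be realised.** This stands as a condition. But they are the rates on which the trial is sized, and a primary method should work at them.
- **The analysis plan may hold a fallback, and analysts are blinded.** Both may be true, and the article is not faulted for leaving a fallback out. The point is the method that it does fix. A fallback suits rare failures; here it would be used in most trials and would in effect become the primary analysis. One triggered only by non-convergence would also leave the Wald interval in place where the fit does converge. Blinding lessens the worry about a late choice of estimator but does not repair coverage.

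**Conclusion.** The point holds in this form: the primary method named in section 2.14 is a poor choice for the design in sections 2.9 and 2.11. At the plan's rates and cell sizes the maximum lies on the boundary in about 82-88% of trials, standard IRLS usually does not deliver a regular fit, and the usual Wald 95% interval covers about 89-91% for the paroxetine-stratum RR. The non-paroxetine RR keeps about 95%, and the interaction-model point estimates are sound. This is moderate undercoverage plus unreliable fitting, not an unusable analysis.

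The figures assume fixed center indicators, equal recruitment of 52 per center as planned, and response close to the stated rates. With clearly lower response in the paroxetine stratum, the boundary becomes uncommon.

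**What to change.** In section 2.14, keep the adjusted RR with its 95% confidence interval and the same terms: treatment, center, paroxetine stratum and treatment x paroxetine. Name one of these as the primary method in place of the log-binomial model:

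- modified Poisson regression with robust standard errors; or
- logistic regression followed by standardisation to the RR.

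Apply the chosen method in each imputed dataset and pool as usual. Only modified Poisson was simulated in the working above.

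The cost is wording in the protocol and analysis plan. The small downside is that robust or delta-method standard errors replace model-based ones. Sample size, data collection and the effect measure do not change. The amendment should be made before outcome data are analysed.

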#### Inclusion criteria

2.3.1

Participants meeting all of the following criteria will be eligible for enrollment:Aged between 18 and 80 years, regardless of gender;Diagnosis of depression according to the Diagnostic and Statistical Manual of Mental Disorders, Fifth Edition criteria, confirmed by licensed psychiatrists at participating centers;Mild to moderate depression, defined as a HAMD-17 score of 8–23;Meeting the traditional Chinese medicine syndrome diagnosis of liver qi stagnation according to the Guidelines for the Diagnosis and Treatment of Depressive Disorders by Integrating Chinese and Western Medicine (Liu et al., 2025), as assessed by licensed traditional Chinese medicine practitioners;Histologically confirmed NSCLC, classified as stage I-IIIA according to the 8th edition of the American Joint Committee on Cancer staging system;Having undergone radical lung cancer resection, with no more than 6 months elapsed since surgery;Expected survival time ≥6 months as assessed by the treating oncologist;Karnofsky Performance Status (KPS) score ≥70;No previous use of antidepressant medication before enrollment.

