#### Primary outcome

2.6.1

The primary outcome of this trial is the total effective rate at the end of the 6-week treatment period, defined as the proportion of participants achieving a ≥25% reduction in their HAMD-17 total score from baseline (Wang et al., 2019). The HAMD-17 is an observer-rated instrument designed to assess depressive symptoms in individuals with a clinical diagnosis of depression. According to standard thresholds, a HAMD-17 score of 0–7 indicates no depression, 8–16 indicates mild depression, 17–23 indicates moderate depression, and ≥24 indicates severe depression (Zimmerman et al., 2013). Treatment response is categorized into four groups based on the percentage reduction in HAMD-17 scores from baseline: recovery (≥75% reduction), markedly effective (≥50% reduction), improved (≥25% reduction), and ineffective (<25% reduction) (Wang et al., 2019). The total effective rate is defined as the proportion of participants classified as recovered, markedly effective, or improved.

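### The primary responder model leaves out baseline HAMD-17; prespecifying it would be a small gain in precision and in protection against chance imbalance, not the repair of an error

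*Protocol article*

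**What the plan says.** All references are to the protocol article.

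- **Endpoint (2.6.1).** A responder is a participant with a "≥25% reduction in their HAMD-17 total score from baseline" at the end of the 6-week treatment.
- **Population (2.3.1).** "Mild to moderate depression, defined as a HAMD-17 score of 8–23". The baseline score can therefore vary almost threefold.
- **Primary model (2.14).** "The primary outcome (total effective rate) will be analyzed using a log-binomial regression model to estimate the adjusted RR". The covariate list is explicit: "The model will include study center and concomitant paroxetine use as covariates". In addition, "An interaction term between treatment group and paroxetine use will be included". Baseline score is not listed. Baseline severity (mild or moderate) appears for the primary outcome only as a subgroup factor.
- **Mixed models for repeated continuous outcomes, including HAMD-17 (2.14).** "The models will include group, time, group-by-time interaction, and baseline score as fixed effects".
- **Remission and other categorical outcomes (2.14).** Unadjusted chi-square or Fisher tests.
- **Randomisation (2.11).** Stratified by center and paroxetine use, not by severity.
- **Sample size (2.9).** An unadjusted comparison of two proportions in each stratum.

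**The concern.** The same scale is adjusted for its baseline value when analysed as a continuous secondary outcome, but not when it becomes the primary responder outcome. The covariate list is stated outright, so this is a choice the protocol makes and not a detail left to another document.

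Two things could be lost. If baseline predicts response, leaving it out forgoes some precision, in strata sized for 80% power with little to spare. And with 90 or 144 participants per arm and no stratification on severity, a chance difference in baseline between the arms would pass into the primary estimate uncorrected. If that happened, any adjustment added afterwards would be open to the charge of being post hoc.

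**Working it through.** **1. Reproduce the sample size.** Inputs from 2.9: 59.6% vs 37.0% and 91.6% vs 79.0%, two-sided alpha 0.05, 80% power, 15% dropout. Pooled-variance formula, no continuity correction:

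n per arm = [1.960·√(2p̄(1−p̄)) + 0.842·√(p₁(1−p₁) + p₂(1−p₂))]² / (p₁−p₂)²

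- No paroxetine: p̄ = 0.483, n = 75.6, so 76. 76/0.85 = 89.4, so 90 per arm and 180 in total, as stated.
- Paroxetine: p̄ = 0.853, n = 122.8, so 123. 123/0.85 = 144.7, so 145 per arm and 290 in total, against 288 stated. The difference is rounding.

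At 85% retention the power is 80.5% and 79.9%. The planned power is thus reached with no baseline adjustment.

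**2. Possible gain in precision.** The protocol gives no baseline–response association, so it is an assumption here: a logistic model with a normal baseline and a given odds ratio (OR) per SD. The table shows the variance of the log risk ratio, adjusted (standardised) over unadjusted, and the resulting power, Φ[(1.96 + z)/√ratio − 1.96], where Φ(z) is the power from step 1.

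| OR per SD | No paroxetine: ratio | Power | Paroxetine: ratio | Power |
|---|---|---|---|---|
| 1.0 | 1.00 | 80.5% | 1.00 | 79.9% |
| 1.35 | 0.98 | 81.2% | 0.99 | 80.3% |
| 1.65 | 0.95 | 82.5% | 0.97 | 81.1% |
| 2.0 | 0.91 | 84.0% | 0.94 | 82.1% |

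Simulation (600 trials per scenario, 9 centers, interaction term, robust Poisson) gave similar variance ratios: 0.96 and 0.97 at OR 1.65, 0.93 and 0.96 at OR 2.0.

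**3. Which part of that range is plausible.** Assume a baseline mean near 16 and SD 3.5 within 8–23, and a change SD of 4.4 points. That SD comes from the HAMD-24 result cited in 2.9, the only SD given. The share of responder variance explained by baseline is then:

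- change proportional to baseline: 0;
- the same point change at every baseline: 0.012–0.025, with fewer responders at high baseline;
- final score regressing on baseline with slope 0.5 (residual SD 3.8): 0.016–0.032, with more responders at high baseline.

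That is roughly 0–3% of variance, worth about one power point. Even the direction of the association is unknown.

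**4. Chance imbalance.** The two-sided 5% limit for a difference in mean baseline is 1.96·√(2/n) SD. This is 0.32 SD with 76 evaluable per arm and 0.25 SD with 122. The expected unadjusted difference in response rate then becomes:

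| OR per SD | No paroxetine (22.6 points if balanced) | Paroxetine (12.6 points if balanced) |
|---|---|---|
| 1.0 | 22.6 | 12.6 |
| 1.35 | 20.4 to 24.8 | 11.7 to 13.5 |
| 2.0 | 17.8 to 27.3 | 10.6 to 14.6 |

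Adjustment largely removes this shift.

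**5. Cost within the planned model.** In the same simulations, an unconstrained log-binomial fit judged by a strict criterion failed or left the admissible range in about 57–60% of trials without baseline, and in about 78–99% with it. A constrained fit or robust Poisson would avoid most of these failures.

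**The case against.** The best defence is that nothing here is wrong. The model adjusts for both stratification factors, randomisation protects the comparison, and the sample size counts on no gain from baseline. All of that stands. A reader might infer from the omission that the primary analysis is biased or underpowered; step 1 shows that it reaches its stated power as planned, and the imbalance in step 4 is random and not systematic.

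A reader might also infer that baseline must be prognostic because the endpoint is computed from it. That does not follow. A percentage reduction already scales by baseline, and under proportional change the association is nil. Integer scoring does leave some dependence: the smallest qualifying drop is 25% at baselines 8, 12, 16 and 20, but 33% at 9, 31% at 13 and 29% at 17. This is a sawtooth, however. A straight line in baseline explains only about 9% of its variation (baselines 8–23, equal weights), so it is a poor argument for a linear covariate.

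The claim of inconsistency needs limiting too. Only the mixed models adjust for baseline; remission, the nearest binary outcome, is tested unadjusted.

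Finally, the adjustment is not free if the log-binomial model is kept, as step 5 shows. This objection is met only by changing the estimator as well.

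**Conclusion.** The point holds as a minor improvement in efficiency and robustness. It is not a validity error. For ORs of 1.0 to 2.0 per SD, the variance of the log risk ratio falls by 0–9% without paroxetine and 0–6% with it, and power rises by 0 to about 4 points. The change models in step 3 make 0–3% of variance the most plausible range. Larger gains would need a stronger association, for which the protocol offers no support.

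The better reason to adjust is step 4: an imbalance at the 5% limit could move the no-paroxetine difference by about 2 points at OR 1.35 and about 5 points at OR 2.0, and the paroxetine difference by about 1 and 2 points. The ORs, the baseline mean and SD, and the change models are all assumptions. With no association, the benefit is zero.

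**What to change.** In section 2.14, add the baseline HAMD-17 total score as a continuous covariate in the primary model, next to center and paroxetine stratum and with the interaction kept. In the same sentence, state that the adjusted risk ratio will be estimated by logistic regression with marginal standardisation, or by Poisson regression with robust standard errors; name one of the two.

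Do this before recruitment, which section 2.15 anticipates for June 2026. If recruitment has begun, make it a dated amendment while the data are still blinded.

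No new data and no change in sample size are needed. The cost is giving up the log-binomial estimator and slightly more analysis work.

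### The primary model includes a treatment-by-paroxetine term, but the plan does not define which contrast from that model is the single adjusted risk ratio to be tested

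*Protocol article*

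**What the plan says.** Section 2.14 (Statistical analysis) assigns the total effective rate to a log-binomial regression "to estimate the adjusted RR and corresponding 95% confidence interval (CI) between the intervention and control groups". Study center and paroxetine use are covariates. The next sentence reads: "An interaction term between treatment group and paroxetine use will be included to assess the potential moderating effect". No second model is introduced. No reference stratum, coding, contrast or weighting is given. The section then sets one two-sided 0.05 threshold for the primary outcome, without naming the parameter it applies to, and lists two software packages without assigning the primary analysis to either.

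Section 2.9 (Sample size estimation) sizes each stratum on its own. Without paroxetine, "the expected total effective rates were 59.6% for MSNP alone and 37.0% for placebo alone, corresponding to a projected risk ratio of 1.61". With paroxetine, "the expected total effective rates were 91.6% for MSNP plus paroxetine and 79.0% for placebo plus paroxetine", "corresponding to a projected risk ratio of 1.16". On that basis "the required sample sizes were 180 participants for the non-paroxetine stratum and 288 participants for the paroxetine stratum". The Discussion gives the stratification two aims, one for MSNP alone and one for MSNP with standard drug treatment.

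**The concern.** A model with a treatment-by-stratum product term has one treatment effect per stratum. The coefficient printed against treatment depends on how paroxetine use is coded. With reference coding it is the effect in the reference stratum, and its confidence interval and p-value carry information on treatment from that stratum alone.

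This would matter little if the plan expected similar RRs, but it expects 1.61 and 1.16. If an analyst reads the treatment row as the primary result, an unstated coding choice decides which stratum the trial is judged on, and a real effect in the other stratum is not tested. If the choice is made after the data are seen, there are several candidate primary results to choose from.

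**Working it through.** **Inputs (section 2.9).** Rates 59.6% vs 37.0% (90 per arm) and 91.6% vs 79.0% (144 per arm). The calculation was run "with a two-sided alpha of 0.05, 80% power, equal allocation within each stratum, and an assumed dropout rate of 15" per cent.

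**Step 1: reproduce the plan's figures.** Two-proportion formula, pooled variance, no continuity correction:
- Non-paroxetine: 76 per arm; 76/0.85 = 89.4, so 90 per arm and 180 in total. Matches.
- Paroxetine: 123 per arm; 123/0.85 = 144.7, so 145 per arm and 290 in total, against 288 stated. Near enough.
- RRs: 0.596/0.370 = 1.61 and 0.916/0.790 = 1.16. Both match.

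The sample size is not in question.

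**Step 2: what the described model can return.** A log-binomial model was fitted to the expected counts at full enrolment. Center was left out because no center-level rates are given.

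| Quantity read as the adjusted RR | RR | 95% CI |
|---|---|---|
| Treatment coefficient, non-paroxetine as reference | 1.61 | 1.17–2.22 |
| Treatment coefficient, paroxetine as reference | 1.16 | 1.05–1.28 |
| Treatment coefficient, sum-to-zero coding, √(1.611 × 1.159) | 1.37 | 1.16–1.62 |
| Standardised to 180:288 from the interaction model | 1.26 | 1.13–1.41 |
| Coefficient from a model without the product term | 1.20 | 1.09–1.32 |

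Standardised RR: (180 × 0.596 + 288 × 0.916)/468 = 371.09/468 = 79.3%; (180 × 0.370 + 288 × 0.790)/468 = 294.12/468 = 62.8%; 0.793/0.628 = 1.26.

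**Step 3: power after 15% dropout.** Wald test on log RR. For one stratum, variance = (1−p₁)/(n·p₁) + (1−p₂)/(n·p₂), with n per arm; power = Φ(z − 1.96).
- Non-paroxetine, n = 76.5: variance 0.0089 + 0.0223 = 0.0311, SE 0.176, z = 0.477/0.176 = 2.70, power 77%.
- Paroxetine, n = 122.4: variance 0.00075 + 0.00217 = 0.00292, SE 0.054, z = 0.148/0.054 = 2.74, power 78%.
- Standardised RR: variance 0.0011 + 0.0024 = 0.0036, SE 0.0597, z = 0.2325/0.0597 = 3.90, power 97%.

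**Step 4: simulated rejection rates.** 85% retention. Where the effect is in one stratum only, the other stratum has its placebo rate in both arms. Ranges cover repeated runs.

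| Scenario | Coefficient, non-paroxetine ref. | Coefficient, paroxetine ref. | Standardised RR | Log-binomial, no product term |
|---|---|---|---|---|
| Planning rates | 77–81% | 78–81% | 97–98% | 94–96% |
| Effect only with paroxetine | 4–5% | 79–81% | 47–49% | 78–80% |
| Effect only without paroxetine | 77–79% | about 5% | 50–51% | about 19% |

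In the two one-stratum scenarios, the coding alone moves the chance of a positive trial between about 5% and about 80%. The last two columns also differ. On the log scale, the no-product model gives most weight to the paroxetine stratum, where response rates are high. It is not a substitute for standardisation.

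**The case against.** The text never says that the treatment coefficient will be reported as the primary result. It asks for an RR between the two groups and gives the product term its own purpose, the assessment of moderation. An article could well condense a main-effects model followed by a separate interaction test in this way, and coding and fitting order usually belong in the analysis plan, which is not shown. Pooling is also not the only sensible target: the strata are sized separately, and the Discussion gives each its own aim.

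Much of this stands. The follow-on reading is possible, though not stated. It would also leave the primary result as the no-product RR of 1.20, which rejects in only about 19% of trials if MSNP works only without paroxetine.

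A reader might go further and infer that no overall RR exists once the product term is in the model, or that the primary p-value must come from only 180 or 288 participants. The document supports neither. The same model gives a standardised RR of 1.26, and the single-stratum result follows only from reference coding.

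What the objection does not remove is that the article itself fixes two things, one RR and a product term in the only model described, and together they leave the primary result undefined. That is more than detail left for later.

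**Conclusion.** The point holds as a badly fixed primary analysis. Section 2.14 does not define which quantity is the adjusted RR, and at the plan's own rates the candidates run from 1.16 to 1.61. Under reference coding the treatment coefficient has about 80% power for its own stratum and about 5% rejection when the effect lies only in the other. A defined overall contrast, standardised to the planned mix, has about 97–98% power at the planning rates.

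These figures assume the section 2.9 rates, 15% dropout spread evenly over the arms, the planned 180:288 split, and no center effect in the expected-count fit. The one-stratum scenarios are illustrations of what each test can see; the plan does not predict them. Standardisation is not the more powerful choice everywhere: with an effect only under paroxetine, the no-product log-binomial model rejects more often (about 78% against 47%). The case for standardisation is that it answers one stated question for everyone randomised and does not depend on coding.

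**What to change.** In section 2.14 and the analysis plan:

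1. Define the primary estimand as one RR, with the risk difference, in all randomised participants, standardised over the two paroxetine strata. Estimate it from the log-binomial model that keeps the product term, state the weights, and test it once at two-sided 0.05.
2. Report the interaction test and the two stratum RRs as labelled secondary results. The interaction has limited power: at the planning rates the ratio of RRs is 0.72 (95% CI 0.52–1.01 at full enrolment), with about 43% power after dropout.
3. Do not list the no-product model as an equivalent route. If it is wanted, make it a named sensitivity analysis.
4. If the two stratum RRs are meant as the primary results, as the separate sizing suggests, state both and an alpha rule. Two independent tests at 0.05 give 1 − 0.95² = 9.75% family-wise error.

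The cost is a few sentences, with no added patients, visits or data. The choice should be fixed and dated before any unblinded data are seen.
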